**Fig 1 pone.0347305.g001:**
[figure not shown]
Study flow diagram for data collection at recruitment. ECG: Electrocardiogram; ECHO: Echocardiography; ICD: Implantable cardioverter-defibrillator; PBMCs: Peripheral blood mononuclear cells.

### Study population

Participant recruitment began on March 7, 2023, and is expected to be completed by December 2025. Participants are being recruited sequentially during their routine medical visits. Patients using AMIO are identified from the database of individuals monitored by the Clinical Research Laboratory on Chagas Disease at INI-Fiocruz. Only patients who have been receiving AMIO for at least three months will be included, ensuring adequate tissue impregnation with a cumulative dose of 10 g [23].

Inclusion criteria are as follows:

Confirmed diagnosis of CD, based on two serological tests with different methodologies (enzyme-linked immunosorbent assay [ELISA] and chemiluminescence) [14,15];Individuals over 18 years of age;Patients classified within the following CCC stages: A, B1, B2, and C [15].

Exclusion criteria are as follows:

Co-infection (HIV, hepatitis B and C, HTLV, Hansen’s disease, leishmaniasis and paracoccidioidomycosis);Immunosuppression of any nature;Cancer;Patients with stage D of CCC will be excluded due to their complex clinical management, including frequent hospitalizations and medication adjustments, which could affect the study’s feasibility.

Patients meeting the inclusion criteria will be invited to participate in the study, and written informed consent will be obtained from all individuals who agree to enroll.

Importantly, AMIO use was prescribed at medical discretion to treat atrial or ventricular arrhythmias [12], independently of this study, characterizing an observational study design.

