### Study design

This is a mixed (retrospective and prospective) longitudinal observational study designed to evaluate the association between chronic use of amiodarone (AMIO) and the following:

(I)**Primary outcome:** inflammatory profile, serologic reactivity to anti-*T. cruzi* antibody, and parasitic load;(II)**Secondary outcomes:** cardiovascular events (new sustained atrial arrhythmias, new sustained or non-sustained ventricular tachyarrhythmias, stroke, heart failure, atrioventricular block, and cardiovascular hospital admissions), CCC progression, internal cardioverter-defibrillator (ICD) implantation, heart transplantation, all-cause death, and a composite endpoint (including the aforementioned cardiovascular events, disease progression, ICD implantation, heart transplantation, and death).

Patients with CCC who take AMIO (exposed group) will be compared with those who do not take this drug (non-exposed group). To minimize potential confounding, patients will be matched based on the stage of CCC according to the Brazilian Consensus on Chagas Disease (A and B1 *versus* B2 and C), age (<50 years *versus* >50 years), and sex (female *versus* male) [15].

Clinical and laboratory data including blood tests, ECG, transthoracic two-dimensional echocardiography (ECHO), and 24-hour Holter monitoring, will be evaluated at three different time points:

(i)**Retrospective data**: from up to 3 years before the start of the study;(ii)**Baseline/recruitment**: at the time of inclusion in the study;(iii)**Prospective data**: during the 2 years of follow-up after recruitment;

The duration of the study, totaling five years of clinical follow-up, was established considering the CCC progresses at a rate of approximately 2% per year [22]. At recruitment, blood samples will be collected for biochemical and molecular analyses to obtain information related to the study’s primary outcome (Table 1) (Fig 1).

**Table 1 pone.0347305.t001:** AMIO-CHAGAS’s study Chronogram: Enrollment, Interventions and Outcome Assessments.

			Retrospective data	Recruitment	Prospective data
			2020 −2022	2023 - 2025	2025 - 2027
**Primary outcome:**	**Immunomodulatory effect**	Gene expression of CCC progression biomarkers in PBMCs	**–**	**x**	**–**
		Determination of serum levels of cytokines and nitric oxide	**–**	**x**	**–**
	**Trypanocidal effect**	Determination of anti-*T. cruzi* antibody titers	**–**	**x**	**–**
		*T. cruzi*-antigen quantification	**–**	**x**	**–**

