**Secondary outcomes**:	Cardiovascular events	New sustained atrial arrhythmias and new sustained or non-sustained ventricular tachyarrhythmias, stroke, heart failure, atrioventricular block and cardiovascular hospital admissions	**x**	**–**	**x**
	Disease progression	Monitored by echocardiography (ECHO), electrocardiogram (ECG), 24-hour Holter	**x**	**x**	**x**
	ICD implantation	According to the medical prescription	**–**	**–**	**x**
	Heart transplantation	According to the medical prescription	**–**	**–**	**x**
	Death of all-cause	–	**–**	**–**	**x**
	Composite endpoint	–	**–**	**–**	**x**

CCC: Chronic Chagas cardiomyopathy; ECG: Electrocardiogram; ECHO: Echocardiography; ICD: Implantable cardioverter-defibrillator; PBMCs: Peripheral blood mononuclear cells.

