### Statistical analysis

Descriptive statistics were used to summarize the characteristics of the study population. Continuous variables will be presented as medians and interquartile ranges (IQR), and categorical variables as absolute and relative frequencies. Missing data will be assessed for their pattern and mechanism (i.e., missing completely at random (MCAR), missing at random (MAR), or missing not at random (MNAR)). The primary approach to handling missing data will be determined once the dataset is available. Depending on the extent and nature of missingness, appropriate strategies may include multiple imputation, complete case analysis, or sensitivity analyses to evaluate the robustness of the findings. The Shapiro-Wilk test will be used to assess the normality of continuous variables. When distributions deviate from normality, appropriate transformations or non-parametric tests will be applied.

Comparisons of patient characteristics according to AMIO use will be evaluated using the independent Student’s t-test for normally distributed continuous variables or the Mann-Whitney U-test for non-normally distributed data. Categorical variables will be compared using the chi-square test or Fisher’s exact test, as appropriate. Correlations between continuous variables related to the primary outcome will be assessed using Pearson or Spearman correlation coefficients, depending on data distribution. AMIO use and longitudinal changes in continuous variables will be analyzed using mixed linear models, adjusted for the duration of amiodarone use. Analyses of time course outcomes (e.g., cardiovascular events, disease progression, all-cause mortality) will be conducted using Cox proportional hazards regression models adjusted for potential confounders such as age, sex, comorbidities and previous etiologic treatment. Hazard ratios (HRs) and their 95% confidence intervals (CI) will be reported. A two-sided p-value ≤ 0.05 will be considered statistically significant.

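### Amiodarone users need only three months on drug, but a look-back of up to 3 years counts as outcome time, so untreated time and the triggering arrhythmia can be credited to amiodarone

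*Protocol article*

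**What the plan says.** All references are to the protocol article.

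- **Exposure.** Study design sets patients taking AMIO against patients not taking it, as two groups; no change of status over time is described. Study population adds: "Only patients who have been receiving AMIO for at least three months will be included". Sample size gives 45 per group.
- **Indication.** Study population: "AMIO use was prescribed at medical discretion to treat atrial or ventricular arrhythmias".
- **Period.** Study design takes clinical data "from up to 3 years before the start of the study", at recruitment, and "during the 2 years of follow-up after recruitment". It describes the whole as "totaling five years of clinical follow-up".
- **Outcomes.** Table 1 defines cardiovascular events as "New sustained atrial arrhythmias and new sustained or non-sustained ventricular tachyarrhythmias, stroke, heart failure, atrioventricular block and cardiovascular hospital admissions". That row is ticked for the retrospective and prospective columns; disease progression is ticked for all three. The rows for ICD, transplantation, death and the composite are ticked for the prospective column only. The primary laboratory outcomes are ticked at recruitment only.
- **Analysis.** Statistical analysis: "AMIO use and longitudinal changes in continuous variables will be analyzed using mixed linear models"; that sentence goes on to adjust for how long AMIO has been used. Events go into Cox models with covariates such as age, sex, comorbidities and earlier etiologic treatment. No start of the clock, time-varying AMIO term or rule for events before the first dose is given.

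**The concern.** The label is fixed at recruitment, but the outcome period reaches back before it. A user who started AMIO within the look-back brings in time when the drug was not being taken, and the group label classes that time as exposed.

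The indication makes this more than random misclassification. AMIO is started because of an arrhythmia, and new arrhythmias are among the outcomes. When the triggering arrhythmia falls in the look-back, the event that caused the exposure can be analysed as an event under exposure. Non-users have no such built-in event. Neither the matching factors (stage, age, sex) nor the listed Cox covariates name arrhythmia history, and adjustment would not repair an outcome that precedes its exposure.

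At stake are the hazard ratios for cardiovascular events and progression, and the longitudinal ECHO and ECG comparisons, where values recorded before AMIO can enter as part of the AMIO group's course.

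**Working it through.** **Step 1. The plan's own figure.** Look-back 3 years + prospective follow-up 2 years = 5 years (60 months). This matches the stated total, so the look-back is part of the follow-up.

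**Step 2. Untreated time in a user.** With m months of AMIO at recruitment and the look-back counted from recruitment, the untreated share is (36 − m)/36 of the look-back and (36 − m)/60 of the total.

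| Months on AMIO | Untreated look-back months | Share of look-back | Share of 5 years |
|---|---|---|---|
| 3 | 33 | 91.7% | 55% |
| 12 | 24 | 66.7% | 40% |
| 24 | 12 | 33.3% | 20% |
| 36 or more | 0 | 0% | 0% |

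Table 1 can also be read as a fixed calendar window, 2020–2022 (366 + 365 + 365 = 1,096 days). "Participant recruitment began on March 7, 2023, and is expected to be completed by December 2025". A user recruited on the first day with three months of AMIO started about 7 December 2022, so 1,071/1,096 = 97.7% of the window is untreated. One recruited at the end of 2025 with three months of AMIO has 100% untreated. On this reading only a start before 2020 gives zero.

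**Step 3. Can the triggering arrhythmia qualify?** The indication is an atrial or ventricular arrhythmia. The outcome is a new sustained atrial arrhythmia, or a new ventricular tachyarrhythmia whether sustained or not. The two overlap without being identical. A first arrhythmia inside the look-back is new in that window, so the word does not exclude it.

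**Step 4. How many users might be affected?** The article gives no distribution of AMIO duration. As an illustration, if starts are uniform from 3 months to 10 years before recruitment, (3 − 0.25)/(10 − 0.25) = 28% of users, about 13 of 45, started in the window. If uniform from 3 months to 5 years, (3 − 0.25)/(5 − 0.25) = 58%, about 26 of 45. Not every such start need follow a qualifying arrhythmia, so the next step uses 10%, 25% and 50%.

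**Step 5. Size of the bias when AMIO does nothing.** Simulation: 45 against 45, true hazard ratio 1, first events at a constant assumed background rate, 5 years of follow-up. The triggering arrhythmia is placed uniformly over the first 2.75 years in the given share of users and counted as an event. Cox model with exposure only, 400 replicates. Entries are the median hazard ratio, with the proportion of replicates at p ≤ 0.05.

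| Share of users with the triggering arrhythmia in the window | Background 5%/year | 10%/year | 15%/year |
|---|---|---|---|
| 0% | 0.95 (5%) | 0.98 (7%) | 1.00 (6%) |
| 10% | 1.52 (14%) | 1.27 (8%) | 1.15 (7%) |
| 25% | 2.26 (53%) | 1.71 (39%) | 1.43 (23%) |
| 50% | 4.02 (98%) | 2.57 (91%) | 2.09 (81%) |

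**Step 6. After the repair.** With the clock started at recruitment, every user has already had at least three months of AMIO, so no pre-treatment months enter. The simulated hazard ratio over 2 years is 0.99 to 1.03, with 1% to 6% of replicates at p ≤ 0.05.

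**The case against.** The strongest reply is that nothing in the article says the Cox clock starts in the look-back. An analysis plan that is not shown could set it at recruitment, and Table 1 gives some support: the composite contains the cardiovascular events and progression yet is ticked as prospective only, and death can only be counted from recruitment. A reader might infer that the plan definitely scores the triggering arrhythmia as an AMIO event. The documents do not go that far. What remains is that the article itself ticks these two outcomes for the retrospective period and counts that period as follow-up. An origin at recruitment would depart from what is published, so the point does not rest on silence alone.

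Second, the mixed models adjust for duration of AMIO use. If duration is computed at each visit it is zero before the first dose and would separate untreated from treated values. The article does not say whether it is visit-specific, so the fault there is possible, not shown. The clause does not extend to the Cox models.

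Third, a reader might infer that AMIO will be made to look harmful throughout. For arrhythmia events that direction follows. For ECHO and ECG it does not: the stated indication is arrhythmia, not falling ejection fraction, so the direction there is unknown.

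Fourth, the larger hazard ratios need many recent starters who all have a qualifying, counted arrhythmia. That is fair. At 10% the distortion is modest, and long-term users add none when the look-back runs from recruitment.

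Finally, the study calls itself exploratory and its primary outcome is measured once, at recruitment. That limits the reach of the point but does not answer it for the outcomes affected.

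**Conclusion.** The point holds, conditionally. As written, the plan combines a fixed exposure label, a three-month entry rule, and a look-back of up to 3 years in which cardiovascular events and progression are outcomes. For users who started AMIO inside that window, this allows untreated time to be classed as exposed and the prescribing arrhythmia to be scored against the drug.

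It reaches cardiovascular events, progression and the longitudinal ECHO and ECG models. It does not reach the primary biomarkers, or ICD, transplantation, death and the composite as ticked in Table 1.

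The arithmetic on untreated time is firm: 33 of 36 look-back months at the minimum, none at 36 months or more when counted from recruitment. The size of the bias is not firm, because the article gives no AMIO durations and no cardiovascular event rate. Under assumed background rates of 5–15% a year and no true effect, the hazard ratio would be about 1.15–1.5, 1.4–2.3 or 2.1–4.0 if 10%, 25% or 50% of users have the triggering arrhythmia in the window and it is counted.

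**What to change.** State the time origin and the exposure coding before the event data are analysed. Either option works for the Cox models.

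1. **Simplest.** Start event follow-up at recruitment in both groups and use the look-back only as baseline history, including arrhythmia history. This also drops time during which both groups must, by design, have survived to be recruited.
2. **Keeps the look-back.** Code AMIO as time-dependent from the recorded start date. Do not count the arrhythmia that led to the prescription as an outcome at all: charging it to untreated time would only turn the bias round.

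In the mixed models, code AMIO as on or off, or as duration to date, at each ECHO and ECG.

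In Table 1, reconcile the composite (prospective only) with its component events (also retrospective), and say whether the look-back runs from each patient's recruitment or over 2020–2022.

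**Cost.** A few sentences and one start date per user, from records already being extracted; duration of use is needed for the mixed models anyway. Option 1 leaves 2 instead of 5 years of event time, at most 45 × 2 = 90 instead of 45 × 5 = 225 person-years per group. Option 2 loses less, but fewer retrospective events and visits count as exposed.

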**Discussion:**

Given the limited literature on the potential trypanocidal and immunomodulatory effects of AMIO in CCC, the findings of this study may provide new insights into the therapeutic potential of AMIO beyond its established antiarrhythmic properties.

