Amiodarone (AMIO) is the most commonly used antiarrhythmic drug in CCC primarily prescribed for abnormalities in the cardiac conduction system [12], and is considered effective in reducing both atrial and ventricular arrhythmias [15,16]. This drug is a class III antiarrhythmic according to the Vaughan Williams classification, and its mechanisms of action include inhibition of potassium, calcium, and sodium channels, thereby prolonging the plateau of the cardiac cell action potential [17,18]. Due to the scarcity of studies involving individuals with CD, the use of AMIO in patients with CCC is based on an expected benefit that should outweigh its adverse effects, such as pulmonary toxicity, polyneuropathy, gastrointestinal discomfort, bradycardia, hepatotoxicity, thyroid dysfunction, and ocular complications [15,19,20]. Therefore, this study will evaluate the potential benefits associated with the use of AMIO in patients with CCC, including possible trypanocidal and immunomodulatory effects of this antiarrhythmic drug.

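### The AMIO group is limited to established users who survived and stayed on the drug, so the secondary hazard ratios do not estimate the effect of starting AMIO; the net direction of bias is unknown

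*Protocol article*

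**What the plan says.** The Study population section of the protocol article identifies exposed patients among people already under follow-up: "Patients using AMIO are identified from the database of individuals monitored by" the centre's Chagas laboratory. It sets a minimum time on drug ("Only patients who have been receiving AMIO for at least three months will be included") and gives the reason ("ensuring adequate tissue impregnation with a cumulative dose of 10 g"). No maximum time on drug is stated. Both groups enter in the same way: "Participants are being recruited sequentially during their routine medical visits". Stage D patients are excluded from both.

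The Study design section defines the groups by current use only: "Patients with CCC who take AMIO (exposed group) will be compared with those who do not take this drug (non-exposed group"). It sets no condition on past AMIO use for the non-exposed group. Matching is on stage, age and sex.

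Table 1 marks ICD implantation, transplantation, death and the composite in the prospective column only. Cardiovascular events and disease progression are marked in the retrospective column as well.

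The Statistical analysis section states adjustment for AMIO duration for the mixed linear models. For the Cox models it names age, sex, comorbidities and previous etiologic treatment as examples of confounders.

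**The concern.** The three-month rule makes sure that the drug has had time to act before blood is drawn, so it serves the primary outcome. For time-to-event outcomes it has a second effect. Patients who start AMIO and then die, or stop because of the toxicities listed in the Background, are removed before they can be counted as exposed. Those who remain have survived and tolerated the drug, for an unlimited time beyond three months. Non-users have passed no equivalent test after a treatment decision. If someone who stopped AMIO is later recruited, nothing in the stated definition keeps that person out of the non-exposed group. If such patients are at higher risk, they raise the comparator's event rate and add to the distortion.

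What is at stake is the meaning of the secondary hazard ratios. The Background says that "this study will evaluate the potential benefits associated with the use of AMIO in patients with CCC", and the Discussion raises a possible mortality benefit of AMIO in CCC. A hazard ratio from established, tolerating users cannot answer whether starting AMIO is beneficial.

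**Working it through.** The protocol gives no figure for early death, early discontinuation or bias, so there is none to reproduce. The check has two parts: what the stated design does to each outcome, and how large the effect could be under declared assumptions.

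**Part 1: the stated design**

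- Being alive and attending a routine visit is required of both groups, so that condition is symmetric. The asymmetry is survival and tolerance after starting AMIO.
- For the prospective-only outcomes (death, ICD, transplantation, composite), every exposed patient enters at least three months after starting AMIO. Here the selection is clearest.
- For cardiovascular events and progression, the retrospective column can bring in earlier events, but only from patients who reached recruitment still on the drug. The selection is reduced, not removed.
- No stated step deals with it. Duration adjustment is given only for the mixed linear models. Adjustment for baseline covariates cannot restore patients who were never eligible.

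**Part 2: possible size (all rates assumed)**

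Suppose a fraction f of patients is frail, with k times the hazard of the rest. The robust hazard is 0.05 per year, follow-up is T = 2 years (from Study design), and the true hazard ratio is 1. A share q of frail AMIO starters is lost before recruitment.

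- Frail share left in the AMIO group: f' = f(1−q) / [f(1−q) + 1 − f]
- Cumulative hazard: H(f) = −ln[f·exp(−0.05kT) + (1−f)·exp(−0.05T)]
- Apparent hazard ratio: H(f') / H(f)

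Worked case, f = 0.20, k = 3, q = 0.25:

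- f' = 0.15 / 0.95 = 0.158
- H(f') = −ln(0.158 × 0.741 + 0.842 × 0.905) = 0.129
- H(f) = −ln(0.20 × 0.741 + 0.80 × 0.905) = 0.137
- Ratio = 0.94

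| f | k | q = 10% | q = 25% | q = 50% |
|---|---|---|---|---|
| 10% | 3 | 0.99 | 0.96 | 0.93 |
| 10% | 5 | 0.98 | 0.94 | 0.88 |
| 20% | 3 | 0.98 | 0.94 | 0.88 |
| 20% | 5 | 0.97 | 0.91 | 0.82 |
| 30% | 3 | 0.97 | 0.93 | 0.85 |
| 30% | 5 | 0.96 | 0.90 | 0.78 |

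Over this grid, total loss among starters is f × q, from 1% (0.10 × 0.10) to 15% (0.30 × 0.50). A simpler formula, 1/(1 − w + wk), takes w as the share of all starters lost and k as their event rate relative to those who remain. It gives 0.91 (w = 10%, k = 2), 0.83 (20%, 2), 0.77 (30%, 2) and 0.63 (30%, 3). The lower values need heavier early loss.

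**Adding the indication.** The Study population section also says that "AMIO use was prescribed at medical discretion to treat atrial or ventricular arrhythmias". Arrhythmia is neither a matching factor nor a named Cox covariate. Let the frail share before any loss be 20% in non-users and higher in AMIO starters, with k = 3:

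| Frail share, AMIO starters | q = 0 | q = 10% | q = 25% | q = 50% |
|---|---|---|---|---|
| 30% | 1.14 | 1.11 | 1.06 | 0.97 |
| 40% | 1.28 | 1.24 | 1.19 | 1.07 |
| 50% | 1.42 | 1.39 | 1.32 | 1.19 |

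Within each row, more early loss moves the ratio toward AMIO. The level of the row depends on the indication, and the protocol fixes neither.

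**Events available.** At the protocol's progression rate of about 2% per year, 90 × 0.02 × 5 = 9 progressions are expected over five years. In the exposed group over the two prospective years, 45 × 0.02 × 2 = 1.8. A few early events missing from one group could therefore matter, and the exposed group cannot usefully be divided by time on drug.

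**The case against.** The case against giving this weight is substantial.

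- A reader might infer that the hazard ratios will favour AMIO overall. The protocol does not support that. Prescribing for arrhythmia can push them the other way, and in the second table most values lie above 1.
- A reader might also infer that follow-up always starts after the early risk period. That fits only the outcomes marked as prospective in Table 1.
- The statement that "the findings of this study may provide new insights into the therapeutic potential of AMIO beyond its established antiarrhythmic properties" comes in the Abstract straight after mention of trypanocidal and immunomodulatory effects, and the Background sentence on potential benefits goes on to name the same effects. Neither refers to hazard ratios. The study calls itself exploratory and speaks of association with chronic use, which is close to the narrower estimand.
- Nothing in the protocol shows that patients who stop for toxicity have a higher cardiac event rate.
- The Cox covariates are given as examples, so an unseen analysis plan may add AMIO duration.
- Deleting the three-month rule would not remove the problem, which comes from enrolling current users.

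These points remove any claim about net direction or size. They leave the mechanism intact: the exposed group is conditioned on survival and continuation after starting AMIO, the comparator is not, and an opposing bias of unknown size does not correct it. Adding AMIO duration to the Cox model would not recover starters who were lost. Chronic use is named as the exposure, but the protocol does not say that the secondary results exclude inference about starting the drug or how former users are handled.

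**Conclusion.** The point holds as a limit on what the secondary hazard ratios can show. Selection of established, tolerating users biases them toward AMIO when taken alone, most clearly for death, ICD implantation, transplantation and the composite. The amount is unknown: the two-class model gives 0.78 to 0.99 at a true hazard ratio of 1, and the simpler formula reaches 0.63 only with 30% of starters lost at three times the event rate. All of these inputs are assumed. Confounding by the arrhythmia indication may act in the opposite direction (0.97 to 1.39 with both forces, again assumed), so the protocol does not determine the net direction. The biomarker outcome, for which the three-month rule was written, is not criticised here.

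**What to change.** 1. Keep the three-month rule for the biomarker outcome.
2. State that the secondary hazard ratios concern continued AMIO use among patients established on the drug and tolerating it, and that they do not estimate the effect of starting AMIO. Word the conclusions to match.
3. Record past AMIO use in the non-exposed group, and repeat the Cox analysis without former users.
4. Where the clinic database records starts and stops, tabulate AMIO starters who stopped, died or reached stage D before recruitment. The protocol says only that current users are identified from it, so this depends on what it holds.
5. Report time on AMIO at recruitment descriptively. Do not present Cox results by duration stratum, because about two progressions are expected among the 45 exposed patients over two years.

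The cost is a narrower claim and some extra record review. Recruitment, the cohort and patient care are unchanged.

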### Sample size

A minimum sample size of 90 volunteers was estimated, with 45 using AMIO and 45 not using AMIO. The sample size calculation for the primary endpoint was based on a study by Rodriguez-Angulo et al., 2017 [26] which evaluated differences in inflammatory markers in individuals with CD treated with AMIO (IFN-γ: 43.75 ± 24.83; TNF-α: 27.08 ± 13.81) compared to untreated individuals (IFN-γ: 84.37 ± 35.08; TNF-α: 52.08 ± 23.38). For the secondary endpoint, sample size calculation was based on a study by Saraiva et al., 2022 [22], which compared LVEF at different stages of CCC (LVEV; Stage A: 68.0 ± 6.4; Stage B: 54.7 ± 9.1; Stage C: 36.7 ± 10.7). Sample size calculations assumed a two-sided significance level of α = 0.05, a statistical power of 80% (1 − β = 0.8), and standard deviations and mean differences derived from these studies. The largest sample requirement among the two endpoints was adopted, and the sample size was increased by 20% to account for potential losses or refusals, resulting in a total of 90 participants.

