### Data collection

Data collection included clinical, immunological, molecular, and imaging parameters, categorized as either categorical or continuous variables. The data generated and analyzed during this study are available from the corresponding author upon reasonable request, subject to ethical and privacy considerations.

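### Three months of amiodarone use does not by itself ensure the 10 g cumulative dose that the protocol says it does

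*Protocol article*

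**What the plan says.** The protocol article, under Study population, admits to the amiodarone group patients "receiving AMIO for at least three months will be included, ensuring adequate tissue impregnation with a cumulative dose of 10 g". The same section explains that "AMIO use was prescribed at medical discretion to treat atrial or ventricular arrhythmias", independently of the study. The inclusion criteria listed there mention neither a daily nor a cumulative dose.

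The Study design section defines exposure as a yes/no contrast: "Patients with CCC who take AMIO (exposed group) will be compared with those who do not take this drug (non-exposed group)". The Sample size section plans for 45 users and 45 non-users.

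Under Statistical analysis, the only amiodarone exposure term beyond user versus non-user is time on the drug: longitudinal changes "will be analyzed using mixed linear models, adjusted for the duration of amiodarone use". Table 1 places every primary-outcome marker at recruitment only.

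**The concern.** A time criterion is presented as guaranteeing a dose. That is true only if every eligible patient's average intake is high enough, and nothing in the article makes it so. The article gives no daily dose, minimum dose, intake condition or check of cumulative dose.

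The point matters because 10 g is the article's own marker that the drug has reached tissue. The immunomodulatory and trypanocidal hypotheses presuppose that it has. A user below that marker is still counted as fully exposed. If such users respond less, the user versus non-user difference is pulled toward zero, and a null result becomes harder to interpret. The duration adjustment does not settle this. It belongs to the models for longitudinal change, whereas the primary markers are measured once, and duration is not dose.

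**Working it through.** **Inputs from the article**
- Minimum time on amiodarone: three months, taken as 90 days (84 and 92 days as alternatives).
- Cumulative dose said to be ensured: 10 g = 10,000 mg.
- Daily dose: not stated.
- Planned users: 45.

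**Can the 10 g be reproduced?** No. Cumulative dose = mean daily intake × days, and the article supplies only the days.

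**Break-even intake.** The lowest mean daily intake at which the minimum duration delivers 10 g is 10,000 mg / days:
- 84 days: 10,000 / 84 = 119 mg per day
- 90 days: 10,000 / 90 = 111 mg per day
- 92 days: 10,000 / 92 = 109 mg per day

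**Illustrative range.** The daily intakes below are assumptions chosen to show the arithmetic. They do not come from the article and are not recommendations.

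| Assumed mean intake (mg/day) | Cumulative dose at 90 days | Days to reach 10 g |
|---|---|---|
| 50 | 4.5 g | 200 |
| 100 | 9.0 g | 100 |
| 150 | 13.5 g | 67 |
| 200 | 18.0 g | 50 |
| 400 | 36.0 g | 25 |

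**Incomplete intake.** The share of a prescribed amount that must actually be taken over 90 days to reach 10 g is 10,000 / (daily amount × 90):
- 150 mg per day: 10,000 / 13,500 = 74%
- 200 mg per day: 10,000 / 18,000 = 56%

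**Who is affected.** A patient must be both close to the three-month minimum and below the break-even intake. At an assumed 100 mg per day the shortfall disappears at day 100, ten days after the minimum. At 50 mg per day it lasts until day 200. Each affected user is 1/45 = 2.2% of the planned exposed group. The article gives no distribution of dose or duration from which to count them.

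**The case against.** The strongest reply is that no number in the article is shown to be wrong. The 10 g appears once, in a subordinate clause giving the reason for the time rule. The sentence carries a reference, and that source may state the dosing on which the link rests. The operative criterion is three months, and the exposed group is consistently defined by it. The Study design section speaks of chronic use, and users are identified from a database of patients under follow-up, so most have probably been on the drug well beyond the minimum. All of this stands, and it limits the size of the problem. It does not make the sentence true. Reading it as two joint conditions (three months and also 10 g) does not help either, because no means of verifying the second is given.

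A reader might also infer more than the documents support:
- **That dose is not collected, so under-dosed users can never be identified.** The itemised variables under Data collection omit dose, but they also omit age, sex, comorbidities and duration of amiodarone use, all of which the models need. The lists are plainly not exhaustive. The section covers clinical parameters in general, and data are extracted from medical records. Non-collection is unproven.
- **That the primary contrast is materially diluted.** Any percentage would need an assumed fraction of users below 10 g and an assumed absence of effect in them. The article gives neither, and treating 9.0 g as no exposure would be extreme.
- **That exposure in the cohort varies as widely as the table above.** Those totals are computed at the eligibility minimum under assumed intakes. They do not describe the enrolled patients.
- **That patients who reach 10 g sooner are wrongly turned away.** A time minimum longer than some patients need is conservative and misclassifies nobody as exposed. Recruitment runs from March 2023 to December 2025, so such patients can qualify later.

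**Conclusion.** The point holds in a narrow form. The article says that a duration rule ensures a cumulative dose, but with discretionary prescribing and no stated dose or check, it does not. A user at the three-month minimum with a mean intake below about 111 mg per day (109 to 119 mg, depending on how three months is counted) is classed as exposed without reaching the article's own 10 g.

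The number of such users is unknown and, if most are long-term users, small. The conclusion rests only on the article's 10 g and three months and on division. The direction of any effect (toward no difference) rests on the further assumption that users below 10 g respond less. The matter deserves correction because the check is cheap and protects the interpretation of a one-time primary comparison. It does not invalidate the design.

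**What to change.** Reconcile the duration rule with the 10 g statement in the Study population section. Then:

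1. Keep the three-month rule as the definition of the main exposed group. Redefining exposure by dose late in recruitment would change the group under study.
2. For each user, take dose, start date and interruptions from the medical record and calculate the cumulative dose up to the recruitment blood sample.
3. Report how many users fall below 10 g, and how many cannot be calculated.
4. Repeat the primary user versus non-user comparison without those below 10 g, as a prespecified sensitivity analysis.
5. Remove *ensuring* unless the calculated doses support it.

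Deleting the phrase alone would tidy the text but leave open whether any users fall short. The cost is some additional chart extraction at a single centre that already extracts clinical data from its records, one extra analysis, and a slightly smaller exposed set in that analysis. This concerns how exposure is classified and described. It implies no view on any patient's dose and proposes no clinical rule.
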